**Exploratory endpoints**
1. Changes in bolus passing determined by temporal videofluoroscopic examination 2. Changes in multichannel surface electromyography findings 3. Changes in tongue pressure 4. Changes in peak expiratory flow 5. Changes in swallowing sound

**Safety**
1. Skin symptoms at the region of electrode attachment 2. Exacerbation of neurological symptoms due to electrical stimulation of the head and neck

### Sample size

2.3

We calculated the required sample size according to preliminary cough tests among patients with neurodegenerative disorders. The proportion of patients with a normal cough reflex after the 1% citric acid challenge required was 28.6%. Assuming that the proportion of patients with a normal cough reflex after 8 weeks of therapy will be 50%, a sample size of 27 participants was estimated, based on an alpha level of 0.10, power of 0.80, and 10% dropout rate.

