### Data analysis and statistical methods

2.5

Safety analysis will include an evaluation of the proportion of patients with skin symptoms and of exacerbation of neurological symptoms in the head and neck due to the electrical stimulation. If these symptoms are found, the therapy will be discontinued. To assess primary and secondary endpoints, the swallowing status of each patient at the time of the initial intervention will be compared with that at the end of the intervention (8 weeks from the initiation of the intervention) or at 8 weeks after the end of the intervention (16 weeks from intervention initiation). Statistical analysis will be performed using JMP statistical software version 16 (SAS Institute Inc., Cary, NC, USA). As appropriate, the statistical significance of intergroup differences will be assessed using χ^2^ test, Mann–Whitney *U* test, or unpaired *t*-test. We will consider p < 0.05 reflective of statistical significance.

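### The sample size rests on alpha 0.10 but significance is judged at p < 0.05, so the stated 80% power does not apply to the test that will be run

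*Protocol article*

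**What the plan says.** Section 2.3 (Sample size) takes 28.6% with a normal cough reflex from preliminary tests in neurodegenerative disorders, assumes 50% after 8 weeks of therapy, and concludes that "a sample size of 27 participants was estimated, based on an alpha level of 0.10, power of 0.80, and 10% dropout rate". It does not say whether 0.10 is one- or two-sided, or which test the formula belongs to.

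Section 2.5 (Data analysis and statistical methods) describes one comparison for the primary endpoint and the secondary ones alike. It says that "the swallowing status of each patient at the time of the initial intervention will be compared with that at the end of the intervention"; week 16 is the other time point. It lists the chi-square, Mann–Whitney and unpaired t-tests, and ends: "We will consider p < 0.05 reflective of statistical significance". It sets no separate level for the primary endpoint and, again, gives no sidedness.

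**The concern.** A power statement holds only for the test and significance level it was computed for. Here 80% is claimed at 0.10, while the only decision threshold in the analysis section is 0.05. Two things follow.

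- A non-significant primary result would be read against a claimed 80% chance of detecting the planned effect, when the real chance at the stated threshold is well below that.
- With two levels in print, a p-value between 0.05 and 0.10 can be reported as positive by citing section 2.3 or negative by citing section 2.5. In an open-label single-arm study, that choice could be made with the results in view.

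**Working it through.** **Inputs (section 2.3).** p0 = 0.286, p1 = 0.50, difference 0.214, power 0.80 (z = 0.8416), dropout 10% applied as n/0.9. Then 27 × 0.9 = 24.3, so about 24 evaluable patients. The threshold of 0.05 comes from section 2.5. Normal quantiles: 1.2816 (one-sided 0.10), 1.6449 (two-sided 0.10, which equals one-sided 0.05), 1.9600 (two-sided 0.05).

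**Step 1: reproduce 27.** One-sample arcsine formula:

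- h = 2·arcsin√0.50 − 2·arcsin√0.286 = 1.5708 − 1.1285 = 0.4423
- n = ((z_α + z_β)/h)² = ((1.2816 + 0.8416)/0.4423)² = 23.05, so 24
- 24/0.9 = 26.7, so **27**, the plan's figure

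**Step 2: the other levels and formulas.** The normal-approximation variants are:

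- null/alternative variance: n = ((z_α√(p0(1−p0)) + z_β√(p1(1−p1)))/0.214)²
- single variance: n = (z_α + z_β)²·p(1−p)/0.214², with p = p1 or p = p0

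Evaluable, then enrolled:

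| Formula | One-sided 0.10 | Two-sided 0.10 / one-sided 0.05 | Two-sided 0.05 |
|---|---|---|---|
| Arcsine | 24 → 27 | 32 → 36 | 41 → 46 |
| Null/alternative variance | 22 → 25 | 30 → 34 | 38 → 43 |
| p1 variance | 25 → 28 | 34 → 38 | 43 → 48 |
| p0 variance | 21 → 24 | 28 → 32 | 35 → 39 |

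Only the one-sided 0.10 column contains or surrounds 27. Two independent proportions at alpha 0.10 would need 47 per group (one-sided) or 64 per group (two-sided), far from 27.

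**Step 3: power with 24 evaluable patients.**

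- Arcsine: Φ(0.4423·√24 − z_α) = Φ(2.167 − z_α)
- Null/alternative variance: Φ((0.214·√24 − z_α·0.4519)/0.5)
- Single variance: Φ(0.214·√24/√(p(1−p)) − z_α)

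| Formula | One-sided 0.10 | One-sided 0.05 | Two-sided 0.05 |
|---|---|---|---|
| Arcsine | 81% | 70% | 58% |
| Null/alternative variance | 83% | 73% | 63% |
| p1 variance | 79% | 67% | 55% |
| p0 variance | 85% | 75% | 64% |
| Exact binomial | 73% (≥ 11/24) | 58% (≥ 12/24) | 58% (≥ 12/24) |

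If all 27 patients were evaluable, power at two-sided 0.05 would be 67% (null/alternative variance) or 65% (exact).

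**Step 4: an outcome where the two levels disagree.** Against a fixed 28.6%, 11 of 24 normal at week 8 gives a one-sided exact p of 0.054. That is significant at one-sided 0.10 and not at 0.05. With 12 of 24, one-sided p is 0.022. One patient separates a result on which the two sections disagree from one on which they agree.

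**The case against.** **The two levels may be the same thing.** Two-sided 0.10 in planning equals one-sided 0.05 in analysis. The document says neither, and one-sample two-sided 0.10 with the stated dropout gives 32 to 38 enrolled, not 27. The nearest rescue is a paired McNemar formula at two-sided 0.10 that assumes no patient worsens (discordant share 0.214). It gives 27 before dropout and 30 after, whereas section 2.3 says dropout is already in the 27. Since the method is unstated, one-sided 0.10 is the best-fitting reading and not a proven one.

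**The study is exploratory and sets no formal success rule.** True: section 2.5 speaks only of statistical significance, and the Discussion calls the study exploratory. That can justify 0.10. It does not explain why the analysis then uses 0.05.

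**The size can be overstated.** Three cautions stand.

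- The exact test has only 73% power even at one-sided 0.10, so the like-for-like exact loss is 73% to 58%; the rest of the gap from 80% is discreteness.
- A chi-square test treating 24 baseline and 24 week-8 results as independent groups has about 33% power at two-sided 0.05, but most of that shortfall comes from ignoring the pairing, which is a separate matter.
- Moving from 7/24 to 12/24 with nobody worse gives p = 0.0625 by exact McNemar but 0.025 by the uncorrected version, so that example depends on the variant chosen.

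None of these removes the contradiction.

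**The full protocol may hold a separate primary level.** Possibly, but condensing for a journal leaves details out. It does not account for two conflicting levels in print.

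**Conclusion.** The plan is wrong as written. It sizes the trial at 0.10 and judges it at 0.05, and the 80% belongs only to the first. With 24 evaluable patients and a one-sample comparison of 28.6% with 50%, approximate power is 55–64% if p < 0.05 is two-sided and 67–75% if it is one-sided; the exact test gives 58% either way. Holding 80% at two-sided 0.05 would take 39 to 48 enrolled, depending on the formula.

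These figures assume a one-sample test against a fixed reference, the reading that reproduces 27. A paired analysis would depend on the share of patients who change status, which the document does not give. For shares from 0.214 to 0.50, McNemar power at two-sided 0.05 with 24 patients is about 64% down to 31%, also below 80%.

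**What to change.** Keep 27 patients. State one alpha, its sidedness and the primary test identically in sections 2.3 and 2.5, in one of two ways:

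1. Keep two-sided p < 0.05 and replace the 0.80 in section 2.3 with the power that 24 evaluable patients give for the named test (about 58% for an exact one-sample test).
2. State in section 2.5 that the primary endpoint alone is judged at one-sided 0.10 and is exploratory, with p < 0.05 for all other endpoints. Check the power for the named test here too: an exact binomial test gives 73%, not 80%.

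The first is easier to defend, because it leaves the published threshold alone. Section 2.6 has the study running from June 2022 to May 2024, so record the choice as a dated amendment made without reference to outcome data.

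The cost is wording only. No patients or visits are added, but either the stated power or the stated error rate becomes less favourable.

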**Methods:**

This single-arm, open-label study aims to evaluate the effectiveness of percutaneous neck interferential current sensory stimulation in enhancing swallowing function in patients with PD. The efficacy and safety of percutaneous neck interferential current sensory stimulation will be investigated for patients diagnosed with PD, based on the Movement Disorder Society criteria, of Hoehn–Yahr stages 2–4. The patients will receive neck percutaneous interferential current sensory stimulation for 20 min twice a week for 8 weeks using a Gentle Stim® (FoodCare Co., Ltd., Kanagawa, Japan) device. Once the intervention is initiated, evaluations will be performed every 4 weeks for a 16-week period. The primary endpoint to be assessed is the proportion of patients with normal cough with 1% citric acid at the end of the intervention (8 weeks after intervention initiation) compared with that at the beginning. This clinical trial will examine the usefulness of percutaneous neck interferential current sensory stimulation in patients with PD. In addition, this study will use novel instruments, such as multichannel surface electromyography and electronic stethoscope, to evaluate swallowing function.

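### The stated 80% power with 27 patients does not carry over to the planned within-patient comparison: not at two-sided 0.05, and at 0.10 only if very few patients lose a normal cough

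*Protocol article*

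**What the plan says.** Section 2.3 bases the size on "preliminary cough tests among patients with neurodegenerative disorders", where 28.6% had a normal cough reflex after 1% citric acid. It assumes 50% after 8 weeks of therapy and concludes that "a sample size of 27 participants was estimated, based on an alpha level of 0.10, power of 0.80, and 10% dropout rate". It gives no formula, sidedness, pairing or rate of change within patients.

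The comparison to be made is described elsewhere. Table 2 gives the primary endpoint as a proportion at week 8, without a comparator. The abstract supplies one: the proportion "at the end of the intervention (8 weeks after intervention initiation) compared with that at the beginning". Section 2.5 says the same at patient level: "the swallowing status of each patient at the time of the initial intervention will be compared with that at the end of the intervention".

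For testing, section 2.5 says that, as appropriate, "the statistical significance of intergroup differences will be assessed using χ^2^ test, Mann–Whitney *U* test, or unpaired *t*-test". All three are tests for independent groups. The threshold is p < 0.05, sidedness not stated, whereas section 2.3 uses 0.10.

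**The concern.** The sizing and the analysis appear to address different questions. A test against a fixed 28.6% carries sampling error from the week-8 proportion only. A comparison with the patients' own baseline carries information only from those whose status changes, so its power depends on the split between gains and losses. A net rise of 21.4 points can come from 21.4% gaining and none losing, or from 35.7% gaining and 14.3% losing, and power differs greatly between the two. Alpha also tightens from 0.10 to 0.05 between the two sections.

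The stake is interpretation. A reader who takes 80% power at face value would treat a non-significant result as fair evidence of no effect on the cough reflex. If the real power is well below that, such a result says little.

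**Working it through.** **Inputs.** From section 2.3: 28.6%, 50%, alpha 0.10, power 0.80, dropout 10%, N = 27. From section 2.5: threshold 0.05. Net change d = 0.50 − 0.286 = 0.214. Completers: 27 × 0.9 = 24.3, taken as 24. The loss rate (normal at baseline, not normal at week 8) is not in the document. It is an assumption, ranged from 0 to 0.286 × 0.50 = 0.143, the value if week-8 status were independent of baseline. Gain rate = loss rate + 0.214.

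**Reproducing 27.** One-sample arcsine formula: n = ((z_α + z_β)/h)², with h = 2·asin(√0.50) − 2·asin(√0.286) = 0.4423.
- One-sided 0.10: ((1.2816 + 0.8416)/0.4423)² = 23.05, so 24; 24/0.9 = 26.7, so 27. This matches.
- Two-sided 0.10: ((1.6449 + 0.8416)/0.4423)² = 31.6, so 32; 32/0.9 = 35.6, so 36. This does not match.
- Two independent groups: 47 (one-sided 0.10) or 64 (two-sided 0.10) per group. Neither matches.

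**Power of the paired comparison, 24 completers.** All outcomes (gains b, losses c, unchanged 24 − b − c) were enumerated from the trinomial distribution. Each was tested by McNemar: exact (binomial with probability ½ on b + c), mid-p, and uncorrected, z = (b − c)/√(b + c). Only results in favour of improvement count.

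| Alpha | Test | Losses 0% | 2% | 5% | 14.3% |
|---|---|---|---|---|---|
| Two-sided 0.05 | exact | 41% | 37% | 32% | 22% |
| | mid-p | 61% | 53% | 45% | 30% |
| | uncorrected | 79% | 62% | 47% | 30% |
| Two-sided 0.10 | exact | 61% | 53% | 45% | 33% |
| | mid-p | 79% | 68% | 58% | 43% |
| | uncorrected | 91% | 75% | 63% | 45% |
| One-sided 0.10 | exact | 79% | 69% | 61% | 48% |
| | mid-p | 91% | 82% | 74% | 58% |
| | uncorrected | 98% | 89% | 78% | 59% |

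At one-sided 0.10 the uncorrected test still has 82% at 4% losses. A one-sided 0.05 test has the same power as the two-sided 0.10 rows.

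**Hand check of the first column at two-sided 0.05.** With no losses, the number gaining is Binomial(24, 0.214). Exact p = 2 × 0.5^b, so b ≥ 6 is needed, probability 41%. Mid-p = 0.5^b, so b ≥ 5, probability 61%. Uncorrected z = √b must exceed 1.96, so b ≥ 4, probability 79%. Power falls from there as losses rise.

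**Other tests at two-sided 0.05.** The unpaired χ² test that section 2.5 names, with 24 against 24, has about 33% power. Even the one-sample test against a fixed 28.6% has only about 63%.

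**The case against.** The strongest reply is that the shortfall is not proved at the alpha used for sizing. McNemar power depends on a loss rate that the document does not give, and a low one rescues the figure. The usual normal-approximation formula for McNemar, n = (z_α·√p_d + z_β·√(p_d − d²))²/d², with 2% losses (p_d = 0.254) and one-sided 0.10, gives (1.2816 × 0.504 + 0.8416 × 0.456)²/0.0458 = 23.2, so 24, and 27 with dropout. The authors could therefore have sized a paired test and reached the same number. This stands: the fixed-reference basis is an inference from the match, and a reader who concluded that 27 patients simply cannot give 80% power would go too far.

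A reader might also infer that 28.6%, which comes from a mixed neurodegenerative sample, will be the benchmark for success, so that a Parkinson's cohort with a higher starting rate could look positive with no effect. The document does not support this. The abstract and section 2.5 both make the patients' own baseline the comparator, and planning from a related population with its source disclosed is ordinary practice.

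The study also calls itself exploratory and small, and an article may leave detail to a fuller plan. That lowers the severity. It does not remove the issue, because a specific power and alpha are stated here and they do not follow from the comparison and threshold stated here.

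**Conclusion.** The point holds in a limited form and should be fixed. The stated 80% does not hold at the section 2.5 threshold if that is two-sided: power is at best 79%, and 22% to 61% with the exact or mid-p test. At 0.10 it holds only under an unstated assumption of very few losses. At one-sided 0.10 that means up to about 2% (mid-p) or 4% (uncorrected), and never with the exact test (79% to 48%). At two-sided 0.10 only the uncorrected test reaches 80%, at or very near zero losses (91% at none, 75% at 2%).

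This rests on the plan's own 28.6% and 50%, 24 completers, and the assumed loss range. The number of completers matters at the margin: if all 27 completed and nobody lost a normal cough, the uncorrected test at two-sided 0.05 would need at least 4 gains from Binomial(27, 0.214), probability 1 − (0.0015 + 0.0110 + 0.0391 + 0.0886) = 86%. That is not the case the plan sizes for. The mismatch of alpha (0.10 against 0.05), and of unpaired tests with a within-patient comparison, needs no assumption; both can be read directly from sections 2.3 and 2.5.

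**What to change.** Keep 27 patients and make these changes:

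1. Use one alpha and one stated sidedness in sections 2.3 and 2.5.
2. In section 2.5, name a paired test for the primary comparison (McNemar, exact or mid-p) in place of the unpaired tests.
3. In section 2.3, state the assumed proportions gaining and losing a normal cough and the power of the named test, shown over a range of loss rates. As an example, with 26.4% gaining and 5% losing (an assumption, not a figure from the document) and 24 completers, power is 32% exact and 45% mid-p at two-sided 0.05; 45% and 58% at two-sided 0.10; and 61% and 74% at one-sided 0.10.
4. Give the expected width of the paired confidence interval. In the same example, the standard error is √((0.314 − 0.214²)/24) = 0.106, so a 95% interval extends about 1.96 × 0.106 = 0.21, or 21 percentage points, either side of the estimated change.
5. State that 28.6% is a planning value and not the comparator.

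The cost is rewording two sections and reporting a less favourable power. No extra patients, visits or measurements are needed.

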### Data acquisition

2.4

Clinical evaluation and diagnosis will be confirmed by two neurologists (MN and HY). The following data will be recorded: body height, weight, body mass index, grip power, calf circumference, disease duration, past medical history, habits of alcohol drinking and smoking, blood pressure, heart rate, oxygen saturation, Unified Parkinson's Disease Rating Scale score [18], medication, Functional Oral Intake Scale score, Eating Assessment Tool-10 score, and blood test values [19]. Cough test, tongue pressure, and peak expiratory flow will be investigated as previously reported [5,20]. Moreover, novel methods, including multichannel surface electromyography, electronic stethoscope, and artificial intelligence system, will be applied. The data will be stored in the Redcap, Electronic Data Capture system. Author YH, who will be blinded to the acquired data, will independently monitor and audit the stored data every week.

### Data analysis and statistical methods

2.5

Safety analysis will include an evaluation of the proportion of patients with skin symptoms and of exacerbation of neurological symptoms in the head and neck due to the electrical stimulation. If these symptoms are found, the therapy will be discontinued. To assess primary and secondary endpoints, the swallowing status of each patient at the time of the initial intervention will be compared with that at the end of the intervention (8 weeks from the initiation of the intervention) or at 8 weeks after the end of the intervention (16 weeks from intervention initiation). Statistical analysis will be performed using JMP statistical software version 16 (SAS Institute Inc., Cary, NC, USA). As appropriate, the statistical significance of intergroup differences will be assessed using χ^2^ test, Mann–Whitney *U* test, or unpaired *t*-test. We will consider p < 0.05 reflective of statistical significance.

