### Study design

2.2

The first draft of the study protocol, of a single-arm, open-label study, was finalized on February 28, 2022, and the draft adhered to the SPIRIT reporting guidelines [16]. The second amended draft was finalized on December 31, 2022. We designed the study to determine the efficacy and safety of percutaneous neck interferential current sensory stimulation for patients with PD, diagnosed according to the Movement Disorder Society criteria, of Hoehn–Yahr stages 2–4 at Hiroshima University Hospital [17]. This study aims to identify the factors associated with swallowing dysfunction and determine the safety of neck percutaneous interferential current sensory stimulation. Therefore, neither randomization nor blinding was used in this study design. The patient inclusion and exclusion criteria are presented in Table 1.

**Table 1 tbl1:** Eligibility criteria.

Inclusion criteria
1. Diagnosis of clinically probable or established PD based on the Movement Disorder Society criteria 2. PD of Hoehn–Yahr stages 2–4 at the time of registration 3. Levodopa dosage remaining unchanged for more than 1 month 4. Age >19 and < 86 years 5. Able to visit the hospital twice a week 6. Able to provide written informed consent

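### Section 2.5 plans a within-patient before/after comparison but names only tests for independent groups

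*Protocol article*

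**What the plan says.** The trial has one arm, and section 2.2 states that "neither randomization nor blinding was used in this study design". The abstract sets the primary endpoint, the proportion with a normal cough reflex to 1% citric acid, "at the end of the intervention (8 weeks after intervention initiation) compared with that at the beginning". For the primary endpoint and the secondary ones, section 2.5 spells out the pairing in these words: "the swallowing status of each patient at the time of the initial intervention will be compared with that at the end of the intervention", or with that at week 16. The exploratory endpoints in Table 2 are likewise within-patient, for example "Changes in tongue pressure".

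For inference, section 2.5 says that "the statistical significance of intergroup differences will be assessed using χ^2^ test, Mann–Whitney *U* test, or unpaired *t*-test", where appropriate, with significance at p < 0.05. It defines no groups and names no McNemar, Wilcoxon signed-rank or paired t-test.

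**The concern.** The χ² test on a two-by-two table of time point by result, the Mann–Whitney U test and the unpaired t-test all treat the two sets of observations as coming from different people. Here they come from the same people. If a patient's two results are positively correlated, which is the usual case, the variance of the before/after difference is smaller than these tests assume. The p-value is then too large, and a real change is more easily missed.

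A trial planned for 27 patients has little power to spare. The choice of test should also be settled in writing before analysis, so that it cannot follow the result.

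**Working it through.** **Inputs.** Section 2.3 gives a reference rate of 28.6%, an expected week-8 rate of 50%, and 27 participants "based on an alpha level of 0.10, power of 0.80, and 10% dropout rate". Section 2.5 gives p < 0.05. Neither section states sidedness. No within-patient correlation is given, so it is varied below.

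**1. The plan's own sample size.** One-sample arcsine formula, one-sided 0.10:

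n = [(z₀.₉₀ + z₀.₈₀) / (2 arcsin√0.50 − 2 arcsin√0.286)]² = [(1.2816 + 0.8416) / (1.5708 − 1.1285)]² = (2.1232 / 0.4423)² ≈ 23.0, rounded up to 24 evaluable.

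With dropout, 24 / 0.90 = 26.7, giving 27, which matches. An independent-groups calculation needs 47 per group at one-sided 0.10, 64 at two-sided 0.10 and 81 at two-sided 0.05. The stated size therefore gives no support to a two-sample χ² test.

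**2. The planned result, analysed both ways.** Take 24 patients, with 7 normal at baseline and 12 at week 8.

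Unpaired χ²: pooled proportion 19/48 = 0.396, difference 5/24 = 0.208, so χ² = 0.208² / (0.396 × 0.604 × 2/24) = 2.18 and p = 0.14. This depends only on the totals.

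McNemar uses the gains b and losses c: χ² = (b − c)² / (b + c). The exact p is twice the binomial tail of the smaller count out of b + c at probability 0.5. The mid-P version subtracts one point probability from the exact p.

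| Gains / losses | Unpaired χ² p | McNemar asymptotic p | mid-P | exact p |
|---|---|---|---|---|
| 5 / 0 | 0.14 | 0.025 | 0.031 | 0.0625 |
| 6 / 1 | 0.14 | 0.059 | 0.070 | 0.125 |
| 8 / 3 | 0.14 | 0.13 | 0.146 | 0.23 |

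For 5 / 0, for example, exact p = 2 × 0.5⁵ = 0.0625 and mid-P = 0.0625 − 0.5⁵ = 0.031. The unpaired test cannot tell these three data sets apart.

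**3. Power at 24 evaluable patients, two-sided 0.05.** Let w be the proportion who go from normal to abnormal. The cell probabilities are: normal at both times 0.286 − w; gain 0.214 + w; loss w; abnormal at both times 0.5 − w. The implied correlation is φ = (0.286 − w − 0.286 × 0.5) / √(0.286 × 0.714 × 0.5 × 0.5) = (0.143 − w) / 0.226. Power is the sum of multinomial probabilities over all tables that each test rejects.

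| Worsening w | φ | Unpaired χ² | McNemar exact | McNemar mid-P | McNemar asymptotic |
|---|---|---|---|---|---|
| 0% | 0.63 | 25% | 41% | 61% | 79% |
| 5% | 0.41 | 30% | 32% | 45% | 47% |
| 10% | 0.19 | 33% | 26% | 35% | 35% |

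**4. Type I error, nominal 0.05.** With no net change and 5% to 15% switching each way, the same enumeration gives a true size of 0.0004 to 0.024 for the unpaired χ² and 0.0007 to 0.017 for exact McNemar. With independent results (φ = 0) the unpaired χ² has size 5.1%, so its shortfall comes from the correlation it ignores.

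**The case against.** The test sentence speaks of intergroup differences and says as appropriate. Section 2.2 and the Discussion also announce a search for factors associated with dysphagia. Unpaired tests suit those between-patient comparisons, and the full protocol and analysis plan are not shown. This reading is possible, but the test sentence belongs to the same paragraph that sets up the before/after comparison and is the only statement of tests there. If it refers only to subgroups, nothing in the section covers the primary comparison.

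The χ² could also be a one-sample test against 28.6%, which is how the sample size reproduces. But the abstract and section 2.5 compare with the patients' own baseline, and 28.6% came from preliminary tests in patients with neurodegenerative disorders.

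Other points of the defence stand:

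- A reader might infer that every endpoint is affected. Pneumonia incidence (secondary endpoint 8) and the safety events are not before/after comparisons.
- A reader might infer that the confidence intervals will be wrong. The article plans none.
- A reader might set 25% against 79% as the cost of the error. The 79% belongs to the asymptotic test with nobody worsening. There it can reject on as few as four discordant pairs, where the exact p is 2 × 0.5⁴ = 0.125. It is not a fair summary.
- Exact McNemar is no cure-all. It is also conservative, it gives 0.0625 for the planned result with no losses, and at 10% worsening its power is below that of χ² (26% against 33%).

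**Conclusion.** The concern holds within those limits. Section 2.5 states a method that does not match the comparison it describes, for the primary endpoint, secondary endpoints 1 to 7 and the exploratory changes. This is a misstatement in the text, not a detail left to another document.

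A reader might fear false claims of benefit. With positive correlation the error runs the other way: a true type I error below nominal and lost power. Against mid-P McNemar the loss is about 36 percentage points if nobody worsens (61 − 25), 15 at 5% worsening (45 − 30) and 2 at 10% (35 − 33). These figures assume 24 evaluable patients, 28.6% to 50%, two-sided 0.05 and the stated range of worsening. The mismatch itself does not depend on them.

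Paired testing does not bring the design to 80% power at two-sided 0.05. By the usual McNemar formula that needs 35 evaluable patients if nobody worsens and 84 if the two results are independent. The difference between the design alpha of 0.10 and the analysis threshold of 0.05 is a separate matter.

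**What to change.** In section 2.5:

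- For the binary before/after endpoints (the primary endpoint and secondary endpoints 1 to 7), name McNemar's test, preferably mid-P because the exact version can be less powerful than χ² when more patients worsen. Report the numbers of gains and losses, and use a paired interval if intervals are reported.
- For continuous changes, name the Wilcoxon signed-rank test or the paired t-test.
- Keep χ², Mann–Whitney U and the unpaired t-test only for comparisons between different patients, such as risk-factor subgroups, and say so.

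The cost is a sentence or two, settled before the data are analysed. No new data, visits or patients are needed.
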